#### Secondary outcomes

The secondary outcomes are hemodynamic stability (hypotension, bradycardia), duration of stay in the ICU and in the hospital, number of patients (in percentage, 95% CI) with a recurrence of PoAF within 2 months and 1 year after surgery, number of patients (in percentage, 95% CI) with a thromboembolic complication within 2 months and 1 year after surgery, number of patients (in percentage, 95% CI) with a hemorrhagic complication within 2 months and 1 year after surgery, and number of patients (in percentage, 95% CI) with an adverse event due to landiolol or amiodarone within 2 months and 1 year after surgery.

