### Sample size {14}

Two groups of 159 patients (318 patients in total) are needed to show an increase from 70 to 85% of patients in sinus rhythm 48 h after the first episode of PoAF [4, 8], using a two-sided α-risk at 5% and a power at 90%. Considering the uncertainty in the effect size, we need to include a total of 350 patients (175 patients per arm).

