## Statistical methods

### Statistical methods for primary and secondary outcomes {20a}

Categorical variables will be described as count, percentages, and 95% confidence interval, and continuous variables will be described as mean (standard deviation) or median [interquartile range], as appropriate. The analysis for the primary outcome will follow the intention-to-treat principle in which all the randomized patients will be analyzed in the assigned group, using the chi-square test or the Fisher exact test. Secondary outcomes will be analyzed with a chi-square test or a Fisher exact test for categorical variables and with a Student’s *t*-test or a Mann–Whitney *U* test for continuous variables according to their distributions. No sub-group analysis is planned. A two-tailed *p* < 0.05 is considered statistically significant. All statistical analysis will be conducted with SAS V9.4 (SAS Institute, Cary, NC).

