### Methods in analysis to handle protocol non-adherence and any statistical methods to handle missing data {20c}

Data from patients who will be pulled out of the study because of refusal to participate, refusal of the follow-up evaluation, or because of any other reasons as decided by the main investigators will be analyzed according to their initial assigned group on an intention-to-treat analysis. We are planning several sensitivity analyses including multiple imputations to deal missing data and potential lost to follow-up.

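### Complications that accumulate over 1 year are compared as crude proportions in the main analysis, which cannot use partial follow-up; imputation for losses is only a sensitivity analysis

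*Protocol article*

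**What the plan says.** All references are to the protocol article.

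- **Outcome definition.** The section on secondary outcomes under {12} lists the "number of patients (in percentage, 95% CI) with a thromboembolic complication within 2 months and 1 year after surgery", and likewise the number "with a hemorrhagic complication within 2 months and 1 year after surgery". Adverse events due to either drug are worded the same way. Each is a percentage with a 95% CI.
- **Test.** Section {20a}: "Secondary outcomes will be analyzed with a chi-square test or a Fisher exact test for categorical variables". No method that uses follow-up time is named.
- **Withdrawn patients.** Sections {18b} and {20c} keep patients who refuse further follow-up in the arm to which they were assigned.
- **Losses.** Sections {20b} and {20c} plan several sensitivity analyses, multiple imputation among them, "to deal missing data and potential lost to follow-up".
- **Size.** Section {14}: "Considering the uncertainty in the effect size, we need to include a total of 350 patients (175 patients per arm"). The increase over 318 is not presented as an allowance for dropout.

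**The concern.** These three outcomes build up over a year, and some patients may be seen for only part of it. A chi-square or Fisher test takes one binary value per patient. For someone last seen event-free at month 4, the 1-year value is unknown. The intention-to-treat sentence settles that patient's arm, not that value.

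If such patients are dropped, their known event-free time is discarded, and so are early events if all lost patients are removed. If they are counted event-free, the percentage is too low. If losses differ between arms, the second choice moves the comparison as well. At stake are the reported 2-month and 1-year percentages, their intervals and the between-arm tests. These outcomes carry weight because the abstract's discussion argues for landiolol partly on reduced anticoagulation and fewer of its complications.

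**Working it through.** **1. The plan's own figure.** "Two groups of 159 patients (318 patients in total") is stated for 70% vs 85%, two-sided 5%, 90% power.

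- Arcsine formula: n = 2(1.960 + 1.282)² / h², with h = 2·asin√0.85 − 2·asin√0.70. This gives 158.7, so 159 per arm.
- Unpooled formula: (0.70×0.30 + 0.85×0.15)(1.960 + 1.282)² / 0.15² = 157.6, so 158. The pooled formula gives 161.

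The figure reproduces. Power for the primary outcome at 175 per arm is 92.3%. None of this is in question; 175 per arm is carried forward.

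**2. Assumptions.** The article gives no 1-year event rate and no loss rate. Main scenario: 175 per arm; risks of 15% vs 6%; half of events in the first 2 months and half spread over the next 10; loss of 0%, 10% or 20%, uniform over 12 months and unrelated to outcome; no deaths.

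**3. Reported risk if lost patients count as event-free.** An early event falls on average at month 1 and is seen before a uniform loss time with probability 1 − 1/12 = 11/12. A late event falls on average at month 7: 1 − 7/12 = 5/12. The average is (11/12 + 5/12)/2 = 2/3, so one third of events among lost patients are missed. Reported risk = 15% × (1 − L/3):

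- L = 10%: 14.5%
- L = 20%: 14.0%

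A variant of dropping keeps lost patients with an observed event and removes the other lost patients. It errs upwards. The chance of a seen event in a lost patient is 15% × 2/3 = 10%, so the reported risk is 14.5/(1 − 0.10×0.90) = 15.9% at 10% loss, and 14.0/(1 − 0.20×0.90) = 17.1% at 20%.

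**4. Power, 15% vs 6%.** Simulated, 3,000 or more trials per scenario; ranges are across runs. Cumulative incidence was a Kaplan-Meier difference with Greenwood variance. Without deaths this has the same point estimate as Aalen-Johansen.

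| Loss | Lost dropped | Lost counted event-free | Cumulative incidence |
|---|---|---|---|
| 0% | about 80% | about 80% | about 80% |
| 10% | 75–76% | 78% | 79% |
| 20% | 69–71% | 75–77% | 76–78% |

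The pooled normal formula gives the same pattern for dropping: 78.7% with n = 175, 74.3% with 157.5 and 69.2% with 140 per arm.

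**5. Other assumed rates** (constant hazard, formula-based).

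- 20% vs 10%: chi-square power is 74.7% with no loss. At 10% loss it is 70.2% (dropped) or 72.4% (event-free); at 20% loss, 65.1% or 69.9%. A log-rank comparison goes from 77.6% to 75.6% and 73.4%. It therefore loses 2.0 and 4.2 points, against 4.5 and 9.6 when patients are dropped.
- 10% vs 5%: power is 42.7% with no loss, and 39.1% (dropped) or 40.8% (event-free) at 10% loss.

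**6. Unequal loss, no true difference.** Risk is 20% in both arms, with constant hazard λ = −ln 0.80 = 0.2231. The chance of an event before a uniform loss time is 1 − 0.20/0.2231 = 0.1037. With 5% loss in one arm and 15% in the other, event-free counting gives 0.95×0.20 + 0.05×0.1037 = 19.5% and 0.85×0.20 + 0.15×0.1037 = 18.6%. That is a spurious difference of about 1 point.

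**The case against.** **The plan has a third route.** Multiple imputation is planned for exactly these losses. A reader might infer that under this plan a lost patient must be either dropped or counted event-free. The documents do not support that for the plan as a whole. It holds for the main analysis only, because imputation is listed as a sensitivity analysis.

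**Loss is only a possibility.** A reader might also infer that substantial loss is expected. The article calls it potential, gives no rate, and attributes the rise from 318 to 350 to effect-size uncertainty. This objection stands, so the size above is conditional.

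**The gain is small.** Against event-free counting, cumulative incidence gains about a point of power at most. This also stands: there the benefit is removal of bias, and the clear power gain is only against dropping.

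**Censoring has its own assumption.** Cumulative incidence is unbiased only if loss is unrelated to outcome. It does not repair informative loss, so imputation is still needed alongside it.

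**Fixed-time percentages fit the outcome definition.** A 1-year risk is a legitimate target, and cumulative incidence estimates that same risk. Table 1 does give all four late outcomes the same time points, but only recurrence has EKG as its measurement. Stroke, embolic ischemia and major bleeding are clinical events that can be dated. The article does not say whether dates are collected, so the fix needs a fallback.

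**The SAP may say more.** It may, but the point concerns a test that the article states, not a detail left out.

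**Conclusion.** The point holds in a limited form. For thromboembolic, hemorrhagic and drug-related adverse events, the stated main analysis cannot use partial follow-up, and the planned remedy for losses is confined to sensitivity analyses.

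With 15% vs 6%, 175 per arm and non-informative loss, dropping costs about 5 points of power at 10% loss and up to 11 at 20%. Event-free counting understates a true 15% by 0.5 to 1.0 point. Loss of 5% vs 15% can produce a difference of about 1 point where none exists (true risk 20% in both arms). All of these rest on assumed event and loss rates, and at zero loss the methods agree.

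The primary outcome at 48 h and its sample size are not affected. Recurrence, measured by EKG, can remain a proportion. This is a worthwhile refinement of secondary analyses and does not threaten the trial's main conclusion.

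**What to change.** In {20a}, for the three complication outcomes:

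- Make the main analysis the cumulative incidence by arm (Aalen-Johansen), with death as a competing event and patients censored at last contact.
- Report the risk difference with 95% CI at 2 months and at 1 year. This keeps the percentages promised under {12}.
- Name one test in advance for each outcome: Gray's test.
- Keep multiple imputation as the sensitivity analysis, aimed at loss that may be related to outcome.
- Leave recurrence as a proportion.

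**Cost.** The eCRF must hold event, death and last-contact dates, and there is modest extra programming. If those dates are not available, make the multiply imputed risk difference at 2 months and 1 year the main analysis instead. Either change should be fixed before outcomes are examined by arm.

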**Discussion:**

The FAAC trial was approved by the Ethics Committee of EST III with approval number 19.05.08. The FAAC trial is the first randomized controlled trial comparing landiolol to amiodarone for PoAF after cardiac surgery. In case of higher rate of reduction with landiolol, this beta-blocker could be the drug of choice used in this context as to reduce the need for anticoagulant therapy and reduce the risk of complications of anticoagulant therapy for patients with a first episode of postoperative atrial fibrillation after cardiac surgery.

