### Objectives {7}

The primary objective is the number of patients in sinus rhythm 48 h after the first episode of POAF after cardiac surgery. The secondary objectives are the hemodynamic tolerance, the ICU and hospital length of stay, and the recurrence of POAF and/or thromboembolic complications and/or hemorrhagic complications and/or number of patients with an adverse event due to landiolol or amiodarone, within 2 months and 1 year after surgery. Table 1 summarizes the objectives and time points.

**Table 1 Tab1:** Objectives

	Outcomes	Measurements	Time points
Primary	Proportion of patient in sinus rhythm at 48 h	Number (percentage) of patients	48 h
Secondary	Hemodynamic tolerance of treatment	Incidence of MAP < 60 mmHg and/or bradycardia as heart rate < 40/min	ICU LOS
	ICU LOS	Total days	ICU LOS
	Hospital LOS	Total days	Hospital LOS
	Recurrence of PoAF	EKG	2 months and 1 year
	Thromboembolic complications	Stroke or embolic ischemia	2 months and 1 year
	Hemorrhagic complications	Active bleeding uncontrollable, with hemodynamic instability, with an urgency treatment, or in a location with functional or vital prognosis	2 months and 1 year
	Adverse events to amiodarone or beta-blockers		2 months and 1 year

*EKG* Electrocardiogram, *ICU* Intensive care unit, *LOS* Length of stay, *MAP* Mean arterial pressure

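### The single p < 0.05 significance rule is not limited to the primary outcome: it also covers 11 or 12 secondary comparisons, where the chance of at least one false significant result is roughly 20-45%

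*Protocol article*

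**What the plan says.** The rule stands in the Protocol article, section {20a}, whose heading covers primary and secondary outcomes together. After the primary analysis, the section turns to the secondaries: "Secondary outcomes will be analyzed with a chi-square test or a Fisher exact test for categorical variables". Continuous secondaries get a t-test or a Mann-Whitney test. The section then closes the matter of significance with one sentence: "A two-tailed *p* < 0.05 is considered statistically significant".

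The outcomes that fall under the rule are listed in two places.

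- Objectives {7} opens its list with "The secondary objectives are the hemodynamic tolerance, the ICU and hospital length of stay, and the recurrence of POAF". Its Table 1 defines hemodynamic tolerance as "Incidence of MAP < 60 mmHg and/or bradycardia as heart rate < 40/min".
- Outcomes {12}, under secondary outcomes, begins: "The secondary outcomes are hemodynamic stability (hypotension, bradycardia), duration of stay in the ICU and in the hospital". It then names four binary outcomes (recurrence, thromboembolic, hemorrhagic and drug-related adverse events), each read at two horizons. One example is "number of patients (in percentage, 95% CI) with a hemorrhagic complication within 2 months and 1 year after surgery".

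The article calls these outcomes secondary. It states no testing order, no gate on the primary result, no adjustment, no preferred time point and no exploratory label. It plans no interim analysis and no subgroup analysis.

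**The concern.** A significance rule tells the reader in advance which results will be called differences between the drugs. Here it gives the same standing to one primary comparison and to every secondary one. Someone who follows the section as written may declare a significant difference in tolerance, length of stay, recurrence, complications or adverse events from a single p-value below 0.05. Nothing in the text makes that depend on the primary result.

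With many comparisons, such a result is fairly likely by chance alone. Four of the outcomes are also read at both 2 months and 1 year, and neither time point is named as the one that counts. An isolated p-value below 0.05 at either could then be reported with the same word, significant, as the primary finding. These outcomes matter to the trial's argument: the introduction gives better hemodynamic stability as part of the case for landiolol, and that is a secondary outcome here.

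**Working it through.** **1. The plan's own figure.** The only error-rate design in the article is for the primary outcome: 70% against 85%, two-sided 5%, 90% power, 159 per arm (Sample size {14}). The arcsine formula reproduces it:

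- h = 2·arcsin(√0.85) − 2·arcsin(√0.70) = 0.364
- n = 2 × (1.960 + 1.282)² / h² = 158.7, so 159 per arm

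There is one primary outcome at one time point, with no interim look and no subgroup test. Its 5% error therefore stands. The article states no familywise error rate for the secondaries, so there is no such figure to reproduce.

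**2. Counting the secondary comparisons** (Objectives {7} with Table 1, and Outcomes {12}).

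| Outcome | Comparisons |
|---|---|
| Hemodynamic tolerance | 1 if composite, 2 if hypotension and bradycardia are tested separately |
| ICU stay, hospital stay | 2 |
| Recurrence | 2 |
| Thromboembolic complications | 2 |
| Hemorrhagic complications | 2 |
| Drug-related adverse events | 2 |
| **Total** | **11 or 12** |

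**3. Independent tests, no true difference anywhere.** P(at least one) = 1 − 0.95^k.

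- k = 11: 1 − 0.95^11 = 43.1%
- k = 12: 1 − 0.95^12 = 46.0%

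**4. Correlated tests.** The outcomes are related and the article gives no correlations, so a range is needed. Assume standard normal test statistics with a common correlation ρ, each called significant when |Z| > 1.96:

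P(at least one) = 1 − ∫ φ(f) · [Φ((1.96 − √ρ·f)/√(1−ρ)) − Φ((−1.96 − √ρ·f)/√(1−ρ))]^k df

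| ρ | k = 11 | k = 12 |
|---|---|---|
| 0 | 43% | 46% |
| 0.3 | 37% | 40% |
| 0.5 | 30% | 32% |
| 0.7 | 22% | 23% |
| 0.8 | 18% | 19% |

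A second structure puts correlation only where it is most expected: within each pair of 2-month and 1-year readings and between the two lengths of stay. For k = 12, hypotension and bradycardia are also given a correlation of 0.3. Simulation (400,000 draws) gives, for k = 11 and k = 12 respectively, 39% and 42% at within-pair correlation 0.7, and 34% and 37% at 0.9.

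**5. Rare events.** Fisher's test is conservative when events are few. At 175 per arm and an assumed event rate of 2%, its actual size is about 1.5%, against 4.5% for the chi-square test. As a bound, suppose the four thromboembolic and hemorrhagic tests never gave a false positive. Then 7 or 8 tests remain:

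- independent: 1 − 0.95^7 = 30.2%, and 1 − 0.95^8 = 33.7%
- 8 tests at ρ = 0.5: 25%; at ρ = 0.8: 16%

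**The case against.** **It may be settled elsewhere.** This is a journal article. The full protocol and an analysis plan may rank, adjust or label the secondaries, and leaving that to them is no fault. This stands as a limit: the missing hierarchy is not itself the finding. The finding is the sentence that is present, which extends significance to every tested outcome. If an analysis plan already narrows it, the two texts need to be aligned.

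**Nothing stated is false.** The article's 5% is the design level for the primary outcome and a per-test threshold. It never promises 5% across the secondaries. This stands in full: the inflation is measured against the per-test level, not against a broken promise.

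**Many secondaries concern safety or tolerance.** By the count of 12, eight do: hypotension, bradycardia, and three kinds of event at two times. Strict familywise control of these could hide harm. This is a good reason not to impose a correction, and the fix does not. It is not a reason to attach the word significant to each of them.

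**A stronger reading that the text does not support.** A reader might infer that the plan intends to rescue a neutral primary result with a secondary finding, because the abstract's discussion speaks of using landiolol to "reduce the risk of complications of anticoagulant therapy for patients with a first episode of postoperative atrial fibrillation". That sentence is conditional on a higher conversion rate with landiolol, which is the primary outcome. It presents the lower anticoagulant risk as a consequence of conversion. It shows no plan to build a claim on secondary tests alone.

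**No single number is given by the document.** Any one figure, such as 30%, depends on an assumed correlation. This also stands, and is why the result is given as a range.

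**Conclusion.** The point holds in a modest form. The significance rule in section {20a} is broader than it should be. Followed as written, it lets any of 11 or 12 secondary comparisons be declared significant, whatever the primary shows. If no secondary outcome truly differs, the chance of at least one such declaration is roughly 20-45%, depending on the correlation assumed. It is somewhat lower if Fisher's test is applied to rare events, but still well above 5% in the cases examined.

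The range rests on three assumptions that the article does not supply: all secondary nulls true, approximately normal test statistics, and the correlations shown.

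The primary conclusion, the sample size and the conduct of the trial are not affected. The result should not be read as showing that the trial's type I error is 30% or 45%: its single primary test keeps its 5%.

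**What to change.** Reword the significance sentence in section {20a}, and carry the same wording into the analysis plan, along these lines:

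> The two-sided 5% significance level applies to the primary outcome only. Secondary outcomes are exploratory. They will be reported as between-arm differences with 95% confidence intervals, without adjustment for multiplicity and without claims of statistical significance. All safety differences will be reported in full.

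Outcomes {12} already commits the binary secondaries to percentages with 95% confidence intervals. The remaining step is to give the interval for the difference between arms and to do the same for the lengths of stay.

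The cost is a few sentences, with no extra patients or data. The article reports that recruitment was still under way, so the wording could be settled before the analysis. The small downside is that an isolated secondary p < 0.05 can no longer be presented as a confirmed difference.

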### Interim analyses {21b}

No interim analysis planned.

### Methods for additional analyses (e.g., subgroup analyses) {20b}

There is no sub-group analysis planned. We are planning several sensitivity analyses including multiple imputations to deal missing data and potential lost to follow-up.

### Methods in analysis to handle protocol non-adherence and any statistical methods to handle missing data {20c}

Data from patients who will be pulled out of the study because of refusal to participate, refusal of the follow-up evaluation, or because of any other reasons as decided by the main investigators will be analyzed according to their initial assigned group on an intention-to-treat analysis. We are planning several sensitivity analyses including multiple imputations to deal missing data and potential lost to follow-up.

### Plans to give access to the full protocol, participant-level data, and statistical code {31c}

The final dataset will be available from the corresponding author upon request.

## Oversight and monitoring

No committee is planned for this trial.

### Composition of the coordinating center and trial steering committee {5d}

The coordinating center is the University Hospital of Caen, which is the sponsor of the FAAC study, including the main investigator (EC), scientific responsible (MOF), clinical research staff (CT), and biostatistics (AB, JJP). Their roles are firstly to ensure the patient’s right protection and data validity via quality control of the trial, in addition to management, analysis and interpretation of data, assistance in writing of the report, and support in the publication. Data collected are sponsor property, and every project of the publication has to be validated by the sponsor before submission and should include the sponsor in the list of authors.

No trial steering committee is formed.

### Composition of the data monitoring committee, its role and reporting structure {21a}

There is no safety monitoring board.

### Adverse event reporting and harms {22}

In France, the competent authority qualified this research as “research with minimal constraint.” This means that adverse events are not reported to the sponsor, only new safety information, i.e., if the investigator considers that the risk–benefit balance of the study should be reviewed.

